# Study design

*Study site and population* -- This study will take place the area of Asembo within 4.25 kilometers of Lwak Hospital where CDC’s IEIP program has ongoing population-based surveillance for infectious disease syndromes.

Since September 2001, KEMRI and CDC have collaborated to operate a demographic surveillance system (DSS) in Bondo and Siaya Districts in Western Kenya. Two rural study sites near Lake Victoria, Asembo and Gem, are covered by the DSS, totaling a population of approximately 130,000 people living in approximately 34,000 households. The area is large (almost 400 km2), culturally homogeneous (95% Luo tribe); subsistence farming and fishing constitute the principal economy. The area has perennial, high-level malaria transmission and a high rate of HIV infection (2003, >10% men, >20% women aged 13-34 years). Other infectious diseases are also common in the area. Consequently, the area has mortality figures that reflect this burden of infectious diseases --- infant mortality rate (120 per 1,000 live births) and a life expectancy at birth of 38 years. The area is one of the most impoverished in Kenya; 60-70% of people live below the poverty line in Siaya and >70% in Bondo (Kenyan Central Bureau of Statistics, 1997). The area has high rates of migration -- in 2002, the rate of out-migration was 115 per 1,000 person-years and in-migration was 124 per 1,000 person-years.

The Lwak surveillance area includes 33 villages, with an approximate enrolled population of 23,000 people. Enrollment of villages began in October 2005 and was completed in June 2006. Homes are visited every two weeks by field workers who enquire about symptoms of key infectious diseases, like diarrhea, respiratory infections and malaria. For key symptoms, like diarrhea, cough and fever, the actual number of days of symptoms are recorded. Some basic measurements, such as temperature and respiratory rate, are taken. Health seeking in the last two weeks is also asked about. This is being done for children and adults.

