## Calculation and comparison of incidence rates

Incidence density rates of diarrheal disease will be calculated as number of new episodes of diarrhea per person-time. Using person-time as the denominator can incorporate information from children who are in the study for only part of the time, contributing less than 1 full year of data, due to out-migration, death or birth. 95% confidence intervals will be calculated around point estimates of incidence rates. Incidence rates for acute respiratory illness and malaria will be calculated in the same way as for diarrhea. The mean number of episodes of diarrhea will be compared between the home zinc and nonhome zinc groups using an ANOVA test accounting for repeat episodes of diarrhea within the same child, accounting for potential confounding variables, such as age and season. Potential confounders of the outcome, such as village of residence and age of the child and malaria coinfection, will be controlled for in the final model.

*Calculation and comparison of time to repeat episode of diarrhea.*

The time before a repeat episode of diarrhea in children who have their first episode of diarrhea will be compared between the home zinc and no home zinc groups. The time to a new episode of diarrhea will be measured as the number of days after the last day of the child’s first episode of diarrhea to the first day of the next episode of diarrhea in that child. This analysis will use as a Cox proportional hazards model, in which the child will be censored after the first day of their first repeat episode of diarrhea.

A secondary analysis will compare the number of repeat diarrheal episodes that occur after the first episode of diarrhea. Mean or median number of repeat episodes will be compared by t-test or Wilcoxon rank sum test depending on the distribution of episodes.

*Comparison of the effect of zinc on the treatment of diarrhea.* The mean duration of diarrheal episodes between children in the home zinc and nonhome zinc groups will be compared using ANOVA controlling for potential confounders such as age and season. Repeat episodes of diarrhea in the same children will be accounted for in the analysis. We will also analyze differences in the severity of diarrhea between groups (severe defined as visiting the clinic) and antibiotic use between groups. This will be done using logistic regression with clinic visit and use of antibiotic as the outcome variable.

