## Sample size.

*Diarrhea Prevalence*.

The below calculations are for our primary study outcome of diarrhea prevalence.

Table 2a. Sample size estimates for various prevalences and reductions. Sample size table assumes a 5% reduction in diarrhea prevalence in the control group with a difference of 15% - 10% between groups.

| Difference in groups | Initial Prevalence in each group | N for each group initially/Total N | N for each group at end of trial/ Total N  (with 15% attrition) |
| --- | --- | --- | --- |
| 15% | 3.6 | 1059/2118 | 900/1800 |
| 14% |  | 1184/2368 | 1006/2012 |
| 13% |  | 1318/2636 | 1120/2240 |
| 12% |  | 1435/2870 | 1219/2438 |
| 11% |  | 1651/3302 | 1403/2806 |
| 10% |  | 3036/6072 | 2580/5160 |

Table 2b. Sample size estimates for various prevalences and reductions Sample size table assumes a 10% reduction in diarrhea prevalence in the control group with a difference of 15% - 10% between groups.

| Difference in groups | Initial Prevalence in each group | N for each group initially/Total N | N for each group at end of trial/ Total N  (with 15% attrition) |
| --- | --- | --- | --- |
| 15% | 3.6 | 1550/3100 | 1317/2634 |
| 14% |  | 1745/3490 | 1483/2966 |
| 13% |  | 1978/3956 | 1681/3362 |
| 12% |  | 2259/4518 | 1920/3840 |
| 11% |  | 2798/5596 | 2378/4756 |
| 10% |  | 4118/8236 | 3500/7000 |

We will assume 3.6 episodes per year of diarrhea in children in the study area, with an average duration of 3 days +/- 1 day. This gives a yearly prevalence of diarrhea of 10.8 days of diarrhea per child per year with a range of 7.2 to 14.4 days. We will also assume that because zinc use will increase gradually in the zinc villages as more children get diarrhea, it will take 6 months to achieve the indicated difference in diarrhea prevalence between the two groups (column 1). In the top table, it is assumed that there will be 5% reduction in diarrhea prevalence in the control group (nonhome zinc group) between the start of the study and end of the study 12 months later, due to the implementation of zinc in the clinic. The bottom table assumes that this reduction in the control group over the 12 months will be 10%.

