# Time frame

*Training.* A two-week training will be conducted to train field workers in administration of consent, questionnaire administration, use of ORS and zinc administration and referral criteria.

*Consent phase.* All eligible households in the 33 selected villages will be offered participation in the surveillance. In each household with a child under 5 years of age, a caretaker of the child must sign an informed consent form allowing participation of the child. The consent phase will take approximately 2 weeks. Community consent will be obtained by having an initial meeting with the chiefs and subchiefs of the area, followed by biannual update meetings. In addition, barazas (talks) will be held with community groups, such as churches and women’s groups, to sensitize them to the project.

*Length of study.* The active phase of the study in whichweekly household visits will be made will last 1 year.

*Expected time to publication.* The study will be analyzed and prepared to submit for publication 6 months after the end of the study.

Ethical considerations

*Risks.* Zinc has been administered to over 35,000 children in the ICDDR.B Cholera Hospital in Dhaka without excess mortality.

Zinc can lead to an increase in vomiting. In one study in Nepali children there was a two-fold increase in vomiting (Strand, 2002). Another recent study in Bangladesh showed that more children vomited in the course of their treatment when taking dispersible zinc tablet than among children who did not get zinc -- overall 20% vomited; 40% due to zinc, 26 % placebo, and 34% due to the illness. (Larson 2005). There was also an increase in regurgitation in children who got zinc versus those who did not (8.6% zinc 4.1% placebo, 1.5% nothing. However, it should be noted that most children who vomited after zinc administration had a history of vomiting within the last 24 hours. Moreover, 91% of children who vomited after zinc administration only vomited once.

A small bruise or mild pain on the finger from where the fingerstick blood sample is taken may develop.

The only other risk of being in the study will be minor inconveniences to the family resulting from the brief amount of time necessary to complete the questionnaires every other week, or on days 3 and 7 after diarrheal episodes.

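### Repeat episodes after the first are compared as raw counts by t-test or Wilcoxon, although time left at risk runs from a few weeks to almost a year

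*Protocol*

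**What the plan says.** Under Data Analysis, the subsection on time to repeat episode first plans a Cox model from the end of a child's first episode to the first repeat. It then adds: "A secondary analysis will compare the number of repeat diarrheal episodes that occur after the first episode of diarrhea". The method is fixed in the next sentence: "Mean or median number of repeat episodes will be compared by t-test or Wilcoxon rank sum test depending on the distribution of episodes". No offset, covariate, person-time denominator or cluster term is mentioned for this count.

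Just above, for incidence rates, the protocol explains why a time denominator is needed: "Using person-time as the denominator can incorporate information from children who are in the study for only part of the time", with such children "contributing less than 1 full year of data, due to out-migration, death or birth". The Study design section describes a mobile population: in 2002 "the rate of out-migration was 115 per 1,000 person-years and in-migration was 124 per 1,000 person-years". Children born during the study join at 2 months of age, and active follow-up lasts 1 year.

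**The concern.** The clock for this count starts at each child's own first episode and stops at study end or departure. A child first ill in month 1 has about eleven months in which to have repeats; one first ill in month 11 has about one. Exposure is therefore unequal even with complete follow-up, and migration, death and late entry widen the spread. The t-test and the Wilcoxon test treat all these children alike.

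Two costs follow. Variation in exposure adds noise that a rate analysis removes. And if the timing of first episodes, entry or loss differs between arms, the counts differ for reasons unrelated to recurrence.

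The test is also to be chosen from the observed distribution, with no rule given. A t-test compares means and a Wilcoxon test compares ranks, so the quantity being estimated is undefined until the data are seen. The analysis supports secondary objective 1, on recurrent diarrhea.

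**Working it through.** **Inputs from the protocol.** Sample size section: "We will assume 3.6 episodes per year of diarrhea in children in the study area, with an average duration of 3 days +/- 1 day". Time frame section: one year of follow-up. The stated yearly prevalence reproduces: 3.6 × 3 = 10.8 days, with range 3.6 × 2 = 7.2 to 3.6 × 4 = 14.4.

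**Time left at risk, full follow-up.** Assume an exponential time to first episode, T, at λ = 3.6 per year and a first episode of d = 3/365 = 0.0082 year that must end within the year, so T < U = 0.9918.

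- Share with a first episode during the year: 1 − e^(−3.6) = 97%.
- Mean of T given T < U: 1/λ − U·e^(−λU)/(1 − e^(−λU)) = 0.2778 − 0.9918 × 0.0281/0.9719 = 0.249 year.
- Mean remaining time R: 1 − 0.249 − 0.008 = 0.743 year, or 8.9 months.
- Percentiles of R: 1st 1.0, 5th 3.3, median 9.7, 95th 11.7 months.
- If 15% of children leave at a uniformly distributed time (the protocol assumes 15% attrition; the uniform timing is an assumption here), the 1st and 5th percentiles fall to 0.5 and 2.1 months.

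**Variance cost.** With one common rate, the raw count has variance λE(R) + λ²Var(R), while a person-time rate carries only λE(R). The ratio is 1 + λVar(R)/E(R).

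- Var(R) = 1/λ² − U²·e^(−λU)/(1 − e^(−λU))² = 0.0772 − 0.0293 = 0.0479.
- Ratio = 1 + 3.6 × 0.0479/0.743 = 1.23.

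Simulation gives the same 1.23, and 1.26 when rates vary between children (gamma, variance 0.3). With 30% of children partially followed the ratios are 1.40 and 1.35. With gamma variance 1 they are 1.24 (full follow-up) and 1.29 (30% partial). A ratio of 1.23 is equivalent to using 1/1.23 = 81% of the sample; 1.40 to using 71%.

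**Error rates and power.** Simulated with 1,500 children per arm (half of the roughly 3,000 in the Sample size section), two-sided 0.05, 15% early leavers unless stated, no village effect and 600 runs. Cells give t-test / Wilcoxon / person-time rate ratio with robust standard error.

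| Scenario | Equal rates | Gamma rates, variance 1 |
| --- | --- | --- |
| No effect, exposure alike | 5 / 4 / 5% | 4 / 4 / 3% |
| No effect, 15% v 25% leave early | 28 / 30 / 4% | 10 / 15 / 6% |
| First-episode rate 15% lower, recurrence unchanged | 24 / 28 / 4% | 6 / 6 / 9% |
| Recurrence 5% lower | 46 / 42 / 57% | 22 / 16 / 25% |
| Recurrence 12% lower | 99 / 99 / 100% | 74 / 60 / 84% |
| First and repeat rates both 12% lower | 100 / 100 / 100% | 73 / 60 / 70% |

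The first three rows are false positives for recurrence; the last three are power. The 15% v 25% split is illustrative: the protocol gives a single attrition figure.

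**The case against.** The strongest reply is that recurrence is already analysed with proper regard to time. The Cox model is the leading recurrence analysis, incidence is per person-time, and the raw count is only supportive. Zinc is given for diarrhea, so a child's first episode normally precedes any zinc and its timing should be similar in both arms. Nothing in the protocol predicts differential loss. With similar exposure the raw-count tests hold their level, as the first row of the table shows.

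Much of this stands. The bias is conditional, and the largest false-positive figures need both unequal attrition and identical rates for all children, whereas the Sample size section says that some children are more prone to repeats. Very short exposure is also a tail: with full follow-up about 1% of children have under 28 days left and 4% under 90. If home zinc lowers first and repeat episodes alike, the t-test loses nothing (73% v 70%), but only because the shorter exposure after a later first episode is then counted as less recurrence.

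The rate model is not perfect either. Restricting to children with a first episode selects on their underlying rate. With strongly varying rates and a 15% difference in first-episode rate alone, the rate ratio is 1.02 and its false-positive rate 9%, against 6% for the counts.

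What does not stand is that the gap is already covered. The Cox model stops at the first repeat, so it does not measure the total number of repeats. Nor is this detail left for an analysis plan: the two named tests cannot carry an offset or the village cluster, so a plan could repair the analysis only by replacing them. Choosing a test by distribution is common wording and is the lesser part of the point.

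**Conclusion.** The concern holds. The protocol fixes a method that ignores time at risk for a count whose exposure is unequal by construction, although it recognises the same problem for incidence. The firm cost is a variance inflation of 23% to 26% with full follow-up, and 35% to 40% if 30% of children are followed for only part of the year. These figures rest on 3.6 episodes per year, exponential waiting times and gamma variance of 0 to 0.3; variance 1 gives 24% to 29%. Bias arises only if exposure differs between arms, and its size then depends on how much rates vary between children. The point concerns a supporting analysis of a secondary objective and leaves the primary comparison untouched. It should be corrected before analysis.

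**What to change.** Replace the t-test or Wilcoxon comparison with a negative binomial or Poisson GEE regression of the number of repeat episodes, with log time at risk after the first episode as offset and village as the cluster. Start time at risk where the Cox model starts, after the last day of the first episode, and end it at study end, out-migration, death or last observation, whichever comes first. Report the rate ratio with its 95% confidence interval and remove the data-dependent choice of test. Add a sentence that the analysis is restricted to children who had a first episode, and read it beside the incidence comparison in all children.

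The cost is analysis wording only. Poisson regression with GEE is already planned for prevalence; here the clustering unit must be the village. The dates needed come from the biweekly visits and the linked demographic surveillance.

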| Ethiopia | 6 days/wk x 6 months | RCT | Stunted and nonstunted | Growth | fever | Significant decrease in stunted, not nonstunted | Umeta, lancet 2000 |
| Burkina Faso | 6 days/wk x 6 months | RCT | From DSS | Malaria | fever | No Difference | Muller, 2001. |
| Lesotho | 90 days daily after admission | RCT | Children admitted with malnutrition | Multiple | fever | Decreased in zn group at 30, 60, 90 days | Makonnen, 2003 |
| Malaria |  |  |  |  |  |  |  |
| Burkina Faso | 6 days/wk x 6 months | RCT | From DSS | Malaria | Various ways | No Difference in incidence or severity | Muller O, 2001. |
| Uganda, Ghana, Tanz, Zambia, Ecuador | Supplement to treatment x 4 days | RCT, n = 1087 | Clinics | Malaria | fever, parasitemia, Hb | No difference | Zinc against Plasmodium group 2002. |
| Gambia | Twice weekly | ?, N=110 | Clinics | Malaria | clinical malaria | 32% reduction | Bates 1993. |

Other treatments, such as antimalarials, have been employed successfully using home-based treatment in Africa (Dunyo SK et al). There have been no studies of home zinc treatment for diarrhea in Africa. However, in Mali a program of community based zinc treatment of diarrhea by community health workers showed high acceptance and compliance by mothers (Ellis AA et al, 2006. Winch PJ et al, 2006). The major problem identified in the Mali project was that often mothers opted to give their children zinc alone when they had diarrhea accompanied by other symptoms, such as fever and cough, which required antimicrobial agents. (personal communication [name] from the nonpublished manuscripted entitled “Lessons learned in a pilot introduction of zinc treatment for childhood diarrhea in Bougoni District, Mali”). This problem was addressed and rectified by re-education of community workers and mothers. This point will need to be emphasized and monitored closely in any program of home-based zinc treatment of diarrhea.

Important questions remain regarding the use of zinc in subSaharan Africa.

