Update on Amendment March 26, 2007: The procurement of zinc has been delayed by the Kenya MOH because of lack of competitive bidders in the tender sent out for this in late 2006. Now it is likely zinc will not arrive in Kenya until late 2007. Until zinc arrives and becomes part of the essential drug kit, the study will provide zinc treatment in the clinic to children coming in with diarrhea. The indications and dosages will those recommended by WHO and the same as will be adopted by the Kenya MOH. Until zinc becomes part of the essential drug kit and available to all children in the clinic, only children who are enrolled in this study will receive zinc. When zinc does become part of the essential drug kit and available in the clinics, the children in the study will continue to receive zinc as before, and nonstudy children will also receive it.

Justification for the study. The use of zinc to treat or prevent diarrhea in Kenya has not been studied. The results of such a study among Kenyan children will be important in providing relevant information to the Ministry of Health to make policy decisions and in building within-country advocacy for scale-up of zinc use and whether to adopt a policy of community use of zinc, in addition to use in the health facilities, for diarrhea treatment. Because access to health care is poor in much of Kenya and most children with diarrhea do not go to health facilities, home-based treatment of diarrhea with zinc could be reach more children, and treat and prevent more diarrhea.

Statement of the null hypothesis. In villages in Western Kenya where children with acute diarrhea are treated (self-prescribed zinc/provided in home) with zinc and ORS at home in addition to the clinic, the prevalence of severe acute diarrhea will be the same as in villages where children with acute diarrhea are treated with zinc and ORS at the clinic only.

Objectives

*Primary*

1. To assess if access to zinc treatment for diarrhea in the home in addition to zinc treatment of diarrhea in the clinic leads to a greater reduction in the prevalence of diarrhea than giving zinc for treatment of diarrhea in the clinic only

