## Secondary

1. To assess if access to zinc treatment for diarrhea in the home in addition to zinc treatment of diarrhea in the clinic decreases the likelihood of recurrent diarrhea episodes
2. To assess if access to zinc treatment for diarrhea in the home in addition to zinc treatment of diarrhea in the clinic leads to a reduction in the prevalence of acute respiratory infections
3. To assess if access to zinc treatment for diarrhea in the home in addition to zinc treatment of diarrhea in the clinic results in reduction in antimicrobial use
4. To assess whether treatment of diarrhea with zinc in the clinic leads to a decrease in diarrhea prevalence from baseline rates of diarrhea before introduction of zinc
5. To assess difference in zinc utilization practices in parent initiated home treatment vs clinic treatment communities
   1. frequency of use and adherence to treatment instructions
   2. who receives zinc
   3. used for what indications
6. To compare cost estimates and estimate cost benefits
7. To assess acceptability and satisfaction with a home treatment program among providers and caretakers

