### Hb 5-11 gm/dl - iron tablet or syrup and folate tablet for 14 days dosed according to age (Hb < 5 gm/dl – referral to hospital.

*Procedures for household visits.*  Field workers will visit each enrolled child every 2weeks. S/he will ask about episodes of diarrhea since the last visit as well as current episodes. S/he will also record symptoms of acute respiratory illness and malaria, as well as any health seeking and medications resulting from these illnesses (Appendix C). S/he will ask about recent or current fever and any health seeking and medications resulting from the recent or current fever. S/he will also inquire about any use of zinc in the last two weeks. The number of days of zinc and number of pills of zinc will be documented. The interviewer will ask to see the zinc blister pack and record how many pills are remaining.

*Administration of zinc*

In the villages/clusters randomized to no home zinc, parents will be instructed by the field workers to take their children to the clinic if they have diarrhea, defined as an episode having 3 or more loose or watery stools (+/-) blood in a 24 hour period. At the clinic, the child will be evaluated by a clinical officer. If the child meets the above definition of diarrhea, they will be given zinc and ORS as described below.

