*Follow-up of cases of diarrhea.* Children identified as having a new episode of diarrhea on the routine biweekly household visit or in the clinic will be visited 7 days later. Referrals will be made on these visits according the criteria listed above under G. A short questionnaire regarding ongoing symptoms and signs of illness, interim health care seeking, and possible side effects to the study medication will be administered (Appendix D). No additional zinc or ORS will be given by the field worker on follow-up visits. If the child is still having significant diarrhea at the follow-up visits, the field worker will instruct the mother to take the child back to the clinic (or to the clinic if they have not gone yet.) The child will next be visited on day 14 according to the regular weekly visit schedule.

*Definition of study outcomes.*

- 1. Diarrhea – A diarrheal day will be considered a day in which the child has 3 or more loose or watery stools. New episodes of diarrhea will be defined as at least one diarrheal day without diarrhea in the previous 72 hours. A severe diarrheal episode will be defined as an episode in which children go to the clinic to receive care for the episode.
  2. Acute Respiratory Infections.
     1. Clinical ALRI - An episode of acute lower respiratory illness (ALRI) will be defined for the home visits as a history of cough or difficulty breathing for > 2 days. An ALRI day will be considered a day that is part of an ALRI episode in which a child has cough or difficulty breathing. New episodes of ALRI will be defined as an ALRI episode without an ALRI day in the previous 72 hours. Acute respiratory infection (ARI) will include any child with cough (of any duration), difficulty breathing, or ear pain and/or discharge.
     2. Pneumonia – Pneumonia and severe pneumonia will be defined for children who visit the clinic and meet the IMCI criteria:
        1. Pneumonia in children < 5 years of age -- Cough or difficulty breathing *and* Respiratory rate > 50/minute for 2-11 month old, >40/minute for 1-4 years
        2. Severe pneumonia in children 1 month - 5 years of age

Cough or difficulty breathing and

- - - - 1. chest indrawing
        2. stridor in a calm child
        3. a general danger sign

Unable to breastfeed or drink

Vomits everything

Convulsions

Lethargy or unconscious

- 1. Malaria -
     1. Clinical malaria – History of fever in the preceding 24-48 hours as reported by the caretaker

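### Diarrhea severity is defined as a clinic visit, which home zinc can change directly, so fewer visits could be reported as milder disease

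*Protocol*

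**What the plan says.** Under Definition of study outcomes, the Protocol states: "A severe diarrheal episode will be defined as an episode in which children go to the clinic to receive care for the episode". The Data Analysis text on the effect of zinc on the treatment of diarrhea repeats this: "We will also analyze differences in the severity of diarrhea between groups (severe defined as visiting the clinic) and antibiotic use between groups". It then fixes the model: "This will be done using logistic regression with clinic visit and use of antibiotic as the outcome variable". Antibiotic use is the planned analysis for secondary objective 3, which asks whether home access "results in reduction in antimicrobial use".

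Under Administration of zinc, the arms reach zinc by different routes. In the clinic-only villages, "parents will be instructed by the field workers to take their children to the clinic if they have diarrhea", and zinc is dispensed there. In the home-zinc villages each child under 5 is supplied with a 10-tablet pack every two months. These parents are also told to attend the clinic for diarrhea, and told that having zinc is no reason to stay away.

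Under Clinic visits, the clinic treats bloody diarrhea with nalidixic acid and non-referred pneumonia with cotrimoxazole or amoxicillin.

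**The concern.** An outcome called severity should measure how ill the child was. This one measures whether the family travelled, and the intervention removes one reason to travel in one arm only. Fewer visits in the home-zinc villages could mean milder illness, or equally ill children kept at home. The planned odds ratio has the same sign in both cases, and the label settles the question in favour of the first.

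The Background describes this behaviour. In the Mali programme, "mothers opted to give their children zinc alone when they had diarrhea accompanied by other symptoms, such as fever and cough, which required antimicrobial" agents. If it recurs here, visits and antibiotic use fall together, and two apparently favourable results could reflect missed care. The trial is meant to help the Ministry of Health decide whether zinc should go into homes, and whether it displaces needed visits bears on that decision.

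**Working it through.** The Protocol gives no rate, power or sample size for clinic visits or antibiotic use, so there is no figure to reproduce. The calculations below show direction and possible scale. Every rate in steps 1 to 3 is an assumption.

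**1. Severity outcome with identical disease in both arms.** Let v be the share of control episodes seen at the clinic and r the share of those visits that home zinc displaces. The home-arm share is v(1 − r).

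- Mid case, v = 0.40 and r = 0.25: home share 0.40 × 0.75 = 0.30. Odds ratio = (0.30/0.70)/(0.40/0.60) = 0.64.
- Range, v from 0.20 to 0.60 and r from 0.10 to 0.50: at the mild end (0.18/0.82)/(0.20/0.80) = 0.88; at the strong end (0.30/0.70)/(0.60/0.40) = 0.29.

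**2. Antibiotic use under the same displacement.** Assume 20% of episodes have an antibiotic indication. If seen, 90% of those and 30% of the others are treated, so use after a visit is 0.2 × 0.9 + 0.8 × 0.3 = 0.42. Assume 10% use without a visit.

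- Control: 0.40 × 0.42 + 0.60 × 0.10 = 0.228.
- Home: 0.30 × 0.42 + 0.70 × 0.10 = 0.196.
- Odds ratio = (0.196/0.804)/(0.228/0.772) = 0.83.
- Indicated but untreated, control: 0.2 × (0.40 × 0.10 + 0.60 × 0.90) = 0.116.
- Indicated but untreated, home: 0.2 × (0.30 × 0.10 + 0.70 × 0.90) = 0.132, a ratio of 1.14.

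The ranges of step 1 were combined with this setting and a second one (10% of non-indicated episodes treated if seen, 5% use without a visit). The antibiotic odds ratio runs from 0.95 to 0.59. Use falls whenever an antibiotic is more likely after a visit than without one.

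**3. What the visit result cannot show.** Suppose visits fall from 40% to 37%, odds ratio (0.37/0.63)/(0.40/0.60) = 0.88, and 20% of episodes have signs that call for care. Three patterns give the same result:

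- Loss only in episodes with signs: 0.2 × 0.25 + 0.8 × 0.40 = 0.37. Episodes with signs and no visit go from 60% to 75%.
- Uniform loss: they go from 60% to 63%.
- Loss only in episodes without signs: 0.2 × 0.40 + 0.8 × 0.3625 = 0.37. They stay at 60%.

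**4. Precision of a table of episodes with signs and no visit.** Half-width of the 95% interval for the arm difference = 1.96 × √(2 × 0.6 × 0.4 × DE / n), with DE = 1 + (n/16.5 − 1) × ICC. The 33 villages give 16.5 per arm. The Sample size section gives 3.6 episodes per child-year. Children per arm are 650 (the Abstract's 1300, halved) or 1,500 (the Sample size section's 3,000, halved). The share of episodes with signs (20% to 60%) and the ICC (0.01 to 0.05) are assumed.

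- n = 650 × 3.6 × 0.2 = 468, ICC 0.05: DE = 2.37, half-width 9.7 points.
- n = 1,500 × 3.6 × 0.6 = 3,240, ICC 0.01: DE = 2.95, half-width 4.1 points.

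**The case against.** The strongest reply is that the label is open: the text says in the same sentence that severe means visiting the clinic, so a reader will see a clinic-visit odds ratio. That limits the harm but does not remove it, because the outcome definition and the planned interpretation both still call the result severity.

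The second reply is that missed care is already watched. Home-zinc parents are told to attend, most firmly when fever or cough is present. Zinc given without care for other symptoms is reviewed every two weeks and answered with re-education. Field-worker referral and free care apply in both arms. Secondary objective 5 compares the arms on "frequency of use and adherence to treatment instructions". All of this stands, and a reader who inferred that the protocol ignores the hazard would be wrong. These safeguards make displacement less likely, but none corrects an outcome that counts attendance as severity.

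Third, the illustration is built on chosen rates. Loss concentrated in children with signs runs against the instructions, and a uniform 3-point change would fall inside the table's own uncertainty. That is fair. Step 3 shows that the visit result is ambiguous, not that the harmful pattern is likely.

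A reader might also infer that antibiotic use must be split by indication, or that objective 3 is defective because it says antimicrobial while only antibiotics are modelled. The document does not support either as a fault. A split is detail for an analysis plan, and the forms would support it poorly: the household form has no medication row and the follow-up form asks only about drugs taken for diarrhea. The two words appear to be used interchangeably, as in the baseline survey, whose description lists antimicrobial use while its form records antibiotics.

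**Conclusion.** The concern holds for the severity outcome. The Protocol fixes severity as attendance, and attendance is directly exposed to the intervention, so following the plan exactly could report milder diarrhea when only care-seeking changed. A fall in antibiotic use would carry the same ambiguity. The bias depends on home zinc replacing visits, and its size cannot be known from the document; the odds ratios above rest wholly on assumed rates.

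Because the null hypothesis says that "the prevalence of severe acute diarrhea will be the same" in both kinds of village, a reader might infer that the primary result is affected too. It is not. The Abstract, the primary objective, the prevalence analysis and the sample size all concern total diarrhea, and the analysis counts diarrheal days per person-time. The problem is confined to secondary results, but it should be corrected because those results inform the policy question.

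**What to change.** 1. Report clinic visits by arm as care-seeking, and remove attendance from the definition of a severe episode.
2. If a severity outcome is wanted, define it from signs that Appendix C already records by day in both arms: stool count, blood in the stool and inability to drink.
3. Add one between-arm table, with village clustering accounted for and a confidence interval, of diarrhea episodes with bloody stool, fever, or cough with difficult or fast breathing that had no clinic visit. Give it as a proportion of such episodes and as a rate per child-year. Read any fall in antibiotic use beside this table and the respiratory infection results, since less respiratory illness would be a real benefit. Because field-worker referral applies to signs found on the day of the visit, the table describes care-seeking over the recall period and does not count breached referrals.
4. Correct the clinic row of Appendix C, which names Akala, to the study clinic, Lwak, so that the table can be built.

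The cost is a changed label, one form correction and one extra table; the signs are already collected. The drawback is precision. With 40% attendance and uniform displacement of a tenth of visits, episodes with signs and no visit would rise from 60% to 64%, a change within even the best half-width of 4.1 points. Displacement of a quarter would give 60% to 70%, just beyond the worst half-width of 9.7 points. Small displacement may therefore be missed, and the table should carry no pass/fail rule.
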